## Abstract

Stroke patients with autonomic dysfunction are more likely to develop cardiac problems, which have been linked to lower functional outcomes and increased mortality. In this study, heart rate variability (HRV) detection paired with the Clinical Feature Scale will be utilized to elucidate the immediate impact of manual acupuncture on autonomic dysfunction of varying severity in the convalescence stroke phase.

This is a randomized, single-blind, controlled clinical trial approach. At a ratio of 1:1, 60 appropriate patients will be randomly randomized into either the experimental or control group. On the basis of symptomatic treatment drugs, the experimental group will additionally undertake acupuncture therapy 3 times a week for 4 weeks, for a total of 12 times. Primary outcomes include 24-hour HRV and 60-minute HRV detection at week 4 compared with baseline. The secondary outcome is the score of clinical feature scale at week 4 compared with the baseline. Adverse events and safety indices will be recorded throughout the experiment. The SPSS V.25.0 statistical program was applied for analysis, and measurement data were expressed as mean ± SD.

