## 3. Interventions

### 3.1. Experimental group

All subjects are able to use basic symptomatic treatment drugs, such as hypotensor, lipid-lowering drugs, hypoglycemic drugs, antiplatelet aggregation drugs, etc.

On the basis of symptomatic treatment drugs, acupuncture will be performed. The patients in the acupuncture group will lie in the prone position. The selected acupoints are Neiguan (PC6), Zusanli (ST36). All acupoints are localized according to the WHO Standard Acupuncture Locations^[18]^ and are exhibited in Table 2 and Figure 2. After accurate positioning and routinely disinfecting the local skin of the patient and the hands of the physician with 75% ethanol, physician will insert sterile disposable acupuncture needles (Hanyi, 0.25 mm × 40 mm) into the selected acupuncture points and apply the manipulation of even reinforcing and reducing movement for 1 minute, the rotating angle is between 60° to 210°, and the depth is 0.5 to 1 cun (1 cun ≈ 20 mm). The needles will be kept for 20 minutes after stimulating the acupuncture points to reach De qi (a compositional sensation including soreness, numbness, distention, and heaviness), which is believed to be an essential component for acupuncture efficacy. Acupuncture will be performed once every other day, 3 times a week, for a total of 12 times.

**Table 2 T2:** Locations and manipulations of acupoints.

Acupoint	Location	Manipulation
Neiguan (PC6)	Between the palmaris longus tendon and the flexor carpi radialis tendon, 2 cun above the transverse stria of the distal carpometacarpus	Puncture perpendicularly to a depth of 0.5–1 cun with even reinforcing and reducing movement for 1 min
Zusanli (ST36)	Three cun directly below Dubi, and 1 finger- breadth lateral to the anterior border of the tibia	Puncture perpendicularly to a depth of 1–2 cun with even reinforcing and reducing movement for 1 min

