## 4. Outcomes

### 4.1. Primary outcome

The primary outcome measure is the HRV detection change, comprising 24-hour HRV detection and 60-minutes HRV detection compared with baseline (0 week) at week 4. 24-hour HRV detection comprises SDNN, SDANN, RMSSD, pNN50%, LF and HF. In addition, patients in the experimental group will be detected for 60 minutes at each time of treatment (from 10 minutes before the start of therapy to 30 minutes after the completion of treatment) to identify the change in LF and HF. The SDNN (the standard deviation of all NN intervals) represents the heart rate variability. SDANN (the standard deviation of the averages of NN intervals in all 5 minutes segments of the entire recording) and LF (power in low frequency range) represent the activity of both the sympathetic nervous system and the parasympathetic nervous system. RMSSD (the square root of the mean of the sum of the squares of differences between adjacent NN intervals), pNN50% (NN50 count divided by the total number of all NN intervals) and HF (power in the high frequency range) represent the activity of the parasympathetic nervous system.

During the HRV test, the patient should be in a supine resting posture to avoid tension, excitement, and deep breathing, and the surrounding environment should be kept calm. The test timing must be between 8 AM to 9 AM on the test day.

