### 4.6. Statistical analysis

The design of the project was in line with a controlled study. According to the requirements of the standard operating procedures (SOP) for clinical research data management, the statisticians are conducted statistics independently, and are separated from the project research designers and operators. The test was designed by collecting information using the CRF scale. SPSS V.25.0 statistical software (IBM SPSS Statistics) will be used for analysis. The measurement data will be tested for normality and homogeneity of variance. For those with normal distribution were expressed as mean ± SD. The paired t-test will be used for comparison before and after treatment, and the 2 independent samples *t* test will be used for comparison between groups. If the variance is not uniform or does not conform to a normal distribution, the Wilcoxon rank- sum test will be used. The chi-square test will be used for counting data. Unless otherwise stated, hypothesis testing was carried out using 2-sided tests. The test level was *α* = 0.05, with *P* < .05 indicating a significant difference.

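### The 60-minute session HRV is named as a primary outcome but recorded in the acupuncture arm only, so it has no randomised comparison and, in Table 1, no week-0 baseline

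*Protocol article*

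**What the plan says.** The abstract states the purpose as to "elucidate the immediate impact of manual acupuncture on autonomic dysfunction of varying severity in the convalescence stroke phase". It then lists the outcomes: "Primary outcomes include 24-hour HRV and 60-minute HRV detection at week 4 compared with baseline". Section 4.1 agrees: "The primary outcome measure is the HRV detection change, comprising 24-hour HRV detection and 60-minutes HRV detection compared with baseline (0 week) at week 4".

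On who is recorded for 60 minutes, section 4.1 is the only text that speaks: "patients in the experimental group will be detected for 60 minutes at each time of treatment". The window runs "from 10 minutes before the start of therapy to 30 minutes after the completion of treatment", and the stated interest is the change in LF and HF. Section 3.1 accounts for the middle of the window: "The needles will be kept for 20 minutes after stimulating the acupuncture points to reach De qi".

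Section 3.2 gives the control group drug treatment and a month of observation. It describes no sham needling, rest session or 60-minute recording. Table 1 marks 60-minute HRV in weeks 1 to 4, without naming an arm and without a mark at week 0. It marks 24-hour HRV and CFS at weeks 0 and 4.

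Section 4.6 plans a paired t test for change over treatment, and a two-sample t test that "will be used for comparison between groups".

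**The concern.** A component of the primary outcome has no comparator. The strength of a randomised trial lies in the contrast between arms, and for 60-minute HRV that contrast does not exist. What remains is a change within treated patients. That change mixes any effect of needling with lying quietly, anticipating the needle and whatever LF and HF do over an hour of rest.

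This matters more because the other outcomes cannot stand in for it. 24-hour HRV and CFS are taken four weeks apart and cannot show what happens around a single session. If a one-arm paired result reached P < .05, nothing in the article would stop it from counting as a positive primary result, although randomisation contributed nothing to it.

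**Working it through.** **Step 1. The plan's own figure.** Section 4.5 gives δ = 531.0, s = 593.7, α = 0.05 and β = 0.1; section 4.6 makes tests two-sided.

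n per arm = 2 × [s × (z₀.₉₇₅ + z₀.₉₀) / δ]² = 2 × [593.7 × (1.960 + 1.282) / 531.0]² = 26.27, rounded up to 27.

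Allowing for 10% loss: 27 / 0.9 = 30 per arm, 60 in all. Both stated figures reproduce. An exact noncentral t calculation gives 89.7% power at 27 per arm, which is close enough to 90%. The calculation presupposes two arms that are both measured.

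**Step 2. Who is measured on what.**

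| Measure | When (Table 1) | Experimental | Control | Two-sample test possible? |
|---|---|---|---|---|
| 24-hour HRV | weeks 0 and 4 | yes | yes | yes |
| CFS | weeks 0 and 4 | yes | yes | yes |
| 60-minute HRV | weeks 1 to 4 | up to 30 patients, each treatment | none described (sections 4.1 and 3.2) | no |

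**Step 3. Is there a baseline?** The abstract and section 4.1 define the primary outcome as week 4 against week 0. Table 1 has no 60-minute recording at week 0, and the recording is tied to treatments, which start in week 1. The contrast as defined has no starting value for this measure.

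**Step 4. What the session can show.** The window is 10 minutes before, 20 minutes of needle retention and 30 minutes after: 10 + 20 + 30 = 60 minutes. The first 10 minutes give each patient a reference, but not one free of settling, anticipation or drift over the rest of the hour. A concurrent control would be needed to take those out.

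**Step 5. Posture.** Section 4.1 requires the HRV test to be done supine. Section 3.1 has acupuncture given prone. One continuous recording that spans the treatment cannot meet both.

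**Step 6. Illustration of size.** The documents give no figure for non-specific change, so the drift d is an assumption, in units of the SD of the within-patient change. With no needling effect and one contrast per patient, the paired t statistic follows a noncentral t distribution with n − 1 degrees of freedom and noncentrality d√n. The table gives the chance that a two-sided test at 0.05 is significant.

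| Assumed drift d | n = 27: d√n | n = 27: P(significant) | n = 30: P(significant) |
|---|---|---|---|
| 0 | 0 | 5.0% | 5.0% |
| 0.2 | 1.04 | 17.0% | 18.5% |
| 0.3 | 1.56 | 32.4% | 35.5% |
| 0.5 | 2.60 | 70.6% | 75.4% |

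**The case against.** **The paired test is inferred.** No section prescribes a test of the minutes before needling against those after. The paired comparison in section 4.6 may refer to the four-week course, and section 4.1 introduces the session recordings as an addition, which could mean that they only supplement the primary outcome. This stands in part. But the abstract and the opening sentence of section 4.1 both name 60-minute HRV as primary, and on the four-week reading the measure lacks a week-0 value as well as a control arm.

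**Conditions are standardised.** Section 4.1 fixes the test at 8 to 9 AM, at rest and in calm surroundings. A reader might infer that time of morning confounds the result. The documents do not support that: clock time is held constant, and only drift within the hour is left.

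**Table 1 does not contradict section 4.1.** A reader might take the unlabelled 60-minute row to mean that both arms are recorded. The 24-hour HRV and CFS rows name no arm either, so the silence shows nothing in either direction.

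**The trial has other aims.** The introduction also covers cumulative effect, feasibility and efficacy. A reader might conclude that the trial cannot answer its question at all. That goes too far: the randomised 24-hour HRV and CFS comparisons bear on efficacy at four weeks and are intact.

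**The drift figures are generic.** This stands. They describe any one-arm paired test, and they use one contrast per patient although 12 sessions are planned. They show how the problem behaves, not how large it is in this trial.

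**Conclusion.** The point holds. 60-minute HRV is named as primary, is recorded in the experimental arm only, and has no week-0 recording in Table 1. The planned between-group test cannot be applied to it: there are up to 30 treated patients and no controls. Any session change in LF or HF is an uncontrolled before-and-after contrast, and no other outcome has the timing to show an immediate effect. As planned, the trial can describe what happens during a session but cannot attribute it to needling.

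The size in this trial is unknown. Under assumed drifts of 0.2 to 0.5 SD, one contrast per patient and n = 27, the false-positive rate of a paired test would run from about 17% to 71%.

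The conclusion is confined to this component. The sample-size figures reproduce, and the between-arm comparisons of 24-hour HRV and CFS are not touched.

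**What to change.** 1. In the abstract and section 4.1, make the between-arm comparison of change in 24-hour HRV from week 0 to week 4 the only primary efficacy outcome.
2. Move the 60-minute session HRV to a single-arm descriptive outcome, and state that no causal claim about an immediate effect will be drawn from it.
3. Mark the 60-minute row of Table 1 as *experimental group only*.
4. Reconcile the supine position for the HRV test (section 4.1) with the prone position for treatment (section 3.1), so that the conditions of the recording are defined.

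Items 1 to 3 cost wording only: no extra patient, visit or recording. Item 4 needs a decision by the investigators. The price is that one measure loses primary status and the immediate-effect aim becomes descriptive.

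If the sponsor wants to keep a causal claim, controls would need a concurrent recording of the same length, clock time and posture. Matching every session would add up to 30 × 12 = 360 recordings, and a rest-only session would still not reproduce anticipation of the needle.

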### 4.2. Secondary outcomes

The secondary outcome measure is the score change in the Clinical Feature Scale compared with baseline at week 4. With a total score of 0 to 18 points, CFS is used to assess the severity of clinical symptoms of autonomic nerve function. According to heart rate, respiration, blood pressure, body temperature, sweating and posture at the time of seizure, it divides the severity of autonomic nerve dysfunction into 4 grades: normal (0 points), mild (1–6 points), moderate (7–12 points), and severe (≥13 points). All patients will be scored at baseline (week 0) and at the end of treatment (week 4), and the changes in scores before and after treatment will be compared.

### 4.3. Adverse events

Investigators should fill in the “Adverse Event Form” for any adverse reactions that occur during the trial of the subjects, and follow up the investigation, record the treatment process and results in detail, until the laboratory tests return to normal and the symptoms and signs disappear. The investigator decides the diagnosis and treatment measures according to the condition, and decides whether to suspend the observation. If a serious adverse event occurs, the unit undertaking the clinical study must immediately take necessary measures to protect the safety of the subjects. Then the investigator should fill in the “Serious Adverse Event Report Form,” reports it to the Ethics Committee within 24 hours, and signs and dates the report.

### 4.4. Data collection, management and monitoring

The investigator fills in the “Case Report Form” for each subject of this trial. Then it will be reviewed by the clinical monitor and handed over to the data administrator for data entry and management. The case report form can only be underlined when making any evidence-based corrections. The modified data should be signed and dated by the investigator, and the original records should not be rubbed or covered.

### 4.5. Sample size

The study was a case-control study in a group design. Patients recovering from stroke with autonomic dysfunction were tested and compared using the HRV index. According to pre-experiment and literature, HRV index means *δ* = 531.0 and overall standard deviation *s* = 593.7, setting *α* = 0.05 and *β* = 0.1. PASS 11 program calculates *N*1 = *N*2 = 27 for experimental and control cases. We predicted 10% non-response. We plan to recruit 60 participants, 30 in each group.

### 4.6. Statistical analysis

The design of the project was in line with a controlled study. According to the requirements of the standard operating procedures (SOP) for clinical research data management, the statisticians are conducted statistics independently, and are separated from the project research designers and operators. The test was designed by collecting information using the CRF scale. SPSS V.25.0 statistical software (IBM SPSS Statistics) will be used for analysis. The measurement data will be tested for normality and homogeneity of variance. For those with normal distribution were expressed as mean ± SD. The paired t-test will be used for comparison before and after treatment, and the 2 independent samples *t* test will be used for comparison between groups. If the variance is not uniform or does not conform to a normal distribution, the Wilcoxon rank- sum test will be used. The chi-square test will be used for counting data. Unless otherwise stated, hypothesis testing was carried out using 2-sided tests. The test level was *α* = 0.05, with *P* < .05 indicating a significant difference.

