#### 2.2..1. Inclusion criteria.

Meet the diagnostic criteria of Western medicine:(1) Patients who meet the diagnostic criteria of cerebrovascular disease adopted by the Fourth National Cerebrovascular Disease Academic Conference in 1995, and confirmed by brain CT and MRI;(2) Collect a 24-hour dynamic electrocardiogram from 8 to 9 am on the same day to 8 to 9 am on the next day, and set HRV parameters SDNN < 50ms, SDANN < 40 ms, RMSSD < 15 ms, PNN50 < 0.75%, LF < 300 ms^2^, HF < 200 ms^2^;The first onset is in the 3rd to 6th month;Patients aged 18 to 90 years old;Patients who have signed informed consent.

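### Patients are selected on low 24-hour HRV, so the planned within-arm before/after tests lean towards improvement; efficacy should rest only on a baseline-adjusted between-arm comparison

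*Protocol article*

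**What the plan says.** **Entry.** Section 2.2.1 of the protocol article asks for one 24-hour ECG ("Collect a 24-hour dynamic electrocardiogram from 8 to 9 am on the same day to 8 to 9 am on the next day") and sets upper limits: "set HRV parameters SDNN < 50ms, SDANN < 40 ms, RMSSD < 15 ms, PNN50 < 0.75"%, LF < 300 ms² and HF < 200 ms². No repeat or confirmatory recording is mentioned.

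**Outcome.** Section 4.1: "The primary outcome measure is the HRV detection change, comprising 24-hour HRV detection and 60-minutes HRV detection compared with baseline (0 week) at week 4". The indices are those used for entry: "24-hour HRV detection comprises SDNN, SDANN, RMSSD, pNN50%, LF and HF". The 60-minute recording is described for one arm only: "patients in the experimental group will be detected for 60 minutes at each time of treatment".

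**Schedule.** Table 1 marks 24-hour HRV at Baseline and week 4, with nothing under Screening. CFS is marked at the same two times. The 60-minute HRV is marked at weeks 1 to 4, with no mark at week 0.

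**Analysis.** Section 4.6 plans two tests in one sentence. The first is within arm: "The paired t-test will be used for comparison before and after treatment". The second is between arms: "the 2 independent samples *t* test will be used for comparison between groups". Both use two-sided 0.05. The section names no baseline covariate. It does not say whether the between-arm test uses week-4 values or changes, or which of the two tests decides efficacy.

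**The concern.** Patients admitted because a measurement was low tend to have a higher value when it is repeated, even with no treatment. If the qualifying recording is also the baseline, that upward drift is part of every patient's change score. A paired test within an arm cannot separate it from a treatment effect.

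Two misreadings are at stake. A significant rise in the acupuncture arm could be reported as benefit. So could a significant result in one arm beside a non-significant result in the other, although that pattern is not a test of the difference between arms. The article invites such a reading: its Introduction describes earlier acupuncture results first as before/after improvement and only then against a control group.

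A lesser matter is that the between-arm test makes no use of the baseline collected for 24-hour HRV and CFS. It therefore leaves chance imbalance in the estimate and gives up some precision.

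**Working it through.** **The plan's own figure.** Section 4.5 gives δ = 531.0, s = 593.7, α = 0.05 and β = 0.1. The two-sample normal formula gives

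n = 2(1.960 + 1.282)²(593.7/531.0)² = 26.27, rounded up to 27 per arm; 27/0.9 = 30 per arm.

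This matches the stated 27 and 60. The calculation is for a between-arm contrast, so the trial is sized for that comparison and not for the paired tests.

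**Inputs for the drift.** From the documents: upper cut-offs on the outcome indices, 27 analysed per arm, two-sided 0.05. Assumed, because the documents do not give them:
- a normal index, in units of its SD before selection;
- the share q of the unselected distribution that lies below the cut-off;
- the test-retest correlation ρ;
- no treatment effect;
- the qualifying recording used as baseline.

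**Formulas.** With cut-off c = Φ⁻¹(q) and λ = φ(c)/q:
- expected rise without treatment = (1 − ρ)λ
- baseline variance after selection: v = 1 − cλ − λ²
- variance of the change = (1 − ρ)²v + (1 − ρ²)
- variance of the week-4 value = ρ²v + (1 − ρ²)
- residual variance under ANCOVA = 1 − ρ²

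**Worked case, q = 0.25 and ρ = 0.7.** c = −0.674, λ = 1.271, v = 0.242.
- Rise = 0.3 × 1.271 = 0.38 SD.
- Variance of change = 0.09 × 0.242 + 0.51 = 0.532.
- Expected paired t is about 0.381/√0.532 × √27 = 2.7, which already exceeds the critical value of about 2.06.

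**Rate of significant improvement in a paired test with no treatment effect** (simulation, 20,000 arms of 27):

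| Selected | ρ = 0.7 | ρ = 0.8 | ρ = 0.95 |
|---|---|---|---|
| lowest 50% | 37% | 26% | 9% |
| lowest 25% | 74% | 55% | 17% |
| lowest 10% | 95% | 83% | 29% |

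The nominal rate in that direction is 2.5%. For the lowest 25% and ρ between 0.7 and 0.9, about 19% to 25% of null trials show acupuncture significant and control not, against about 2.4% nominally (0.025 × 0.975).

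**Between-arm tests in the same setting.** The t-test on week-4 values, the t-test on changes and ANCOVA all reject in about 5% of null trials. The drift is expected equally in both randomised arms and cancels.

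**Precision, q = 0.25 and ρ = 0.7.**
- ANCOVA against change: 0.510/0.532 = 0.96, a gain of about 4%.
- ANCOVA against week-4 values: week-4 variance = 0.49 × 0.242 + 0.51 = 0.628, and 0.510/0.628 = 0.81, a gain of about 19%.

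**The case against.** The strongest reply is that section 4.6 plans a between-group t-test in the same sentence, in a trial randomised 1:1 and sized for that comparison. Nothing says that efficacy will be judged on the paired tests. This stands: a reader might infer that the trial lacks a valid comparison or that its type I error is inflated, and the documents do not support that. An unadjusted two-sample t-test is valid here, and ANCOVA improves on it without correcting an error.

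Other stronger readings also fail.
- **That the paired tests are bound to show improvement.** With high repeatability and a mild cut-off the rate is about 9%.
- **That the qualifying recording is known to be the baseline.** This is inferred from Table 1 and section 2.2.1. If a fresh recording is taken at week 0, most of the drift happens before it.
- **That every one of the six cut-offs must be met.** Section 2.2.1 lists them without saying so.
- **That natural recovery in months 3 to 6 adds to the drift.** The documents give no figure for it, and the Discussion says the dysfunction may last at least 6 to 9 months.
- **That ANCOVA would bring a large gain over change scores.** The familiar (1 + ρ)/2 variance ratio needs equal variances at both times, which entry truncated on the baseline rules out.
- **That a baseline exists for every outcome.** The 60-minute HRV has no week-0 mark.

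It can also be said that naming the deciding test and covariates belongs in an analysis plan that is not shown. That answers the silence on these points. It does not answer the paired significance tests, which the article itself specifies on outcomes used for selection.

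**Conclusion.** The point holds in limited form. The within-arm paired tests on 24-hour HRV are biased towards improvement in both arms and are not evidence that acupuncture works. Over the tabulated range the false-improvement rate is 9% to 95% against 2.5%. Even the mildest case is more than three times nominal. These rates rest on a normal index, on the qualifying recording being the baseline, and on assumed values of selection depth and correlation.

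The between-arm t-test keeps about 5% type I error. Its weaknesses are that it ignores the baseline, leaves the tested variable open and is not named as decisive. The gain from adjustment is modest against change scores and larger if week-4 values were to be tested. The trial's validity is not in question; what needs settling before analysis is which result may support an efficacy claim.

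The 60-minute HRV is a separate case. It is not the selection recording, so the rates above do not apply to it. With recordings described in one arm only and none scheduled at week 0, it still cannot support a between-arm conclusion.

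**What to change.** Amend section 4.6, and any analysis plan, as follows.
- State that efficacy conclusions rest only on the between-arm contrast.
- For 24-hour HRV and for CFS, analyse the week-4 value by ANCOVA on arm and the baseline of the same measure, and report the adjusted difference with its 95% CI.
- Report within-arm changes descriptively, without significance tests.
- Report the 60-minute HRV descriptively and not as evidence of efficacy. ANCOVA cannot be applied to it as scheduled.
- Say in section 2.2.1 or Table 1 whether the qualifying 24-hour recording is also the baseline.

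The cost is wording. The changes need no further patients, recordings or software, since SPSS fits the model and both baselines are already collected.

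### The rank-sum test is the only named fallback for both t-tests, but it is the wrong test for before/after data and no remedy for unequal variances

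*Protocol article*

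**What the plan says.** Section 4.6 of the protocol article sets out the analysis of continuous data in three steps.

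- A preliminary check: "The measurement data will be tested for normality and homogeneity of variance".
- Two tests if the checks are passed. Within patients, "The paired t-test will be used for comparison before and after treatment". Between arms, the independent-samples t "test will be used for comparison between groups".
- One replacement if either check fails: "If the variance is not uniform or does not conform to a normal distribution, the Wilcoxon rank- sum test will be used".

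No signed-rank test, Welch test or transformation is named. Tests are two-sided at 0.05.

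The rule reaches the primary outcome. Section 4.1 defines that outcome as the change in HRV from week 0 to week 4, made up of 24-hour and 60-minute recordings. It describes the 60-minute recordings, taken around each treatment session, for patients in the experimental group only.

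**The concern.** The fallback sentence follows directly on a sentence that names a paired test and an independent-samples test, and it draws no distinction between them. It also has two triggers, non-normality and unequal variance, with one remedy for both. Two of the resulting uses do not fit the test.

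1. **Paired data.** The rank-sum test treats its two samples as independent. Before and after values from the same patient are not, so its null variance is too large when they are positively correlated. The test becomes conservative and gives up the gain from pairing.
2. **Unequal variances.** The null distribution of the rank-sum test assumes the same distribution in both arms. A difference in spread alone disturbs its level, so it does not solve the problem for which it is prescribed.

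The first is the more serious. As section 4.1 describes the 60-minute recordings, there is no control-arm counterpart, so that part of the primary outcome can only be compared within patients. A statistician who followed the text on non-normal LF or HF data would then run the wrong test on it.

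**Working it through.** **Inputs from the protocol article.** Section 4.5: "HRV index means *δ* = 531.0 and overall standard deviation *s* = 593.7", "setting *α* = 0.05 and *β* = 0.1", 27 per group, 30 after 10% non-response. Section 4.6: "hypothesis testing was carried out using 2-sided tests".

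**Inputs that are assumptions.** The before/after correlation ρ (0.3 to 0.9), the distribution shape, the shift used for power in the paired case, and the between-arm SD ratio (2 to 4). The article gives none of these, so each is shown over a range or as a stated scenario.

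**Step 1: the plan's own figure.** Standardised difference = 531.0/593.7 = 0.894. n = 2(1.960 + 1.282)²/0.894² = 26.3, so 27 per group; 27/0.9 = 30. This reproduces. Exact t-test power at 27 is 0.897. The point does not depend on the sample size calculation, but 27 is the natural n for the checks below.

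**Step 2: paired data, by formula.** Let each measurement have SD σ. The mean before/after difference over n pairs has SD σ√(2(1−ρ)/n). A test that ignores pairing uses σ√(2/n) instead, so its z statistic has SD √(1−ρ), not 1.

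- True size = 2[1 − Φ(1.96/√(1−ρ))]. For ρ = 0.3: 1.96/0.837 = 2.34, size 1.9%. For ρ = 0.5: 1.96/0.707 = 2.77, size 0.6%. For ρ = 0.9: 1.96/0.316 = 6.20, size practically 0.
- Shift of 0.5σ with n = 27: unpaired noncentrality = 0.5√(27/2) = 1.84. Power ignoring pairing = Φ((1.84 − 1.96)/√(1−ρ)): about 44% at ρ = 0.3 and 35% at ρ = 0.9. Power using pairing = Φ(1.84/√(1−ρ) − 1.96): about 59% at ρ = 0.3 and above 99% at ρ = 0.9.

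This uses means in place of ranks, so it shows the mechanism and the approximate size only.

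**Step 3: paired data, by simulation of the rank tests themselves.** With normal data, 27 pairs and ρ from 0.3 to 0.9, rank-sum type I error runs from about 2% to 0%. At a 0.5 SD shift its power runs from about 40% to 37%, against 54% to 100% for signed-rank. At ρ = 0.7 the figures are size 0.1% and power 38% against 88%.

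Skewed data give the same picture (lognormal, log-SD 0.8, log-shift 0.35, 27 pairs):

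| ρ | Rank-sum size | Signed-rank size | Rank-sum power | Signed-rank power |
|---|---|---|---|---|
| 0.3 | 0.019 | 0.048 | 0.31 | 0.41 |
| 0.5 | 0.007 | 0.056 | 0.28 | 0.53 |
| 0.7 | 0.001 | 0.049 | 0.25 | 0.74 |
| 0.9 | 0.000 | 0.053 | 0.18 | 0.99 |

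**Step 4: unequal variances between arms.** Normal data, equal means, 27 against 27, 20,000 runs:

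| SD ratio | Rank-sum size | Welch size |
|---|---|---|
| 2 | 0.056 | 0.047 |
| 3 | 0.065 | 0.051 |
| 4 | 0.074 | 0.051 |

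If dropout left 30 against 24, with the larger SD in the smaller arm, rank-sum size would be 6.6% to 8.9% over the same ratios and Welch would stay near 5%. With the larger SD in the larger arm, rank-sum size is 4.7% to 5.8%.

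**Step 5: where the fallback works.** Between arms, with lognormal data of the same shape (log-SD 0.8) and no effect, rank-sum size is 4.8% to 4.9%. For a 1.7-fold effect its power is about 64%, against about 54% for the t-test on raw values and 66% to 67% on logs. At the design shift (531, SD 593.7, 27 per arm) its power is 0.995 against 0.89 for the t-test with lognormal data, and 0.88 against 0.90 with normal data.

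**The case against.** The best defence is that the fallback sentence comes straight after the between-group clause and may be meant for that comparison alone, or that rank-sum is a slip for signed-rank in the paired case. Either is possible, but the text says neither, and no other fallback is given for the paired test. It is also true that the paired error is conservative, and that before/after tests within an arm do not establish an effect of acupuncture against control. Both points limit the harm; neither makes the rule right.

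Some stronger readings are tempting, and the article does not support them.

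- *That skewed HRV data in general will be analysed with the wrong error rate or little power.* Step 5 shows the opposite for the randomised comparison when the arms have similar shape: rank-sum holds its level and gains on the raw t-test.
- *That the fallback is bound to be used because "overall standard deviation *s* = 593.7" exceeds δ, implying marked right skew.* δ is a difference between means, not a mean, so the comparison says nothing about skew. The index is not named, and the outcome is a change, which can be negative. How often the trigger will fire cannot be read from the article.
- *That rank-sum grossly inflates false positives under unequal spread.* With lognormal arms of equal arithmetic mean and log-SD 0.5 against 1.0 (or 0.8), it rejects in about 38% (or 18%) of runs. But the medians then differ by exp(0.375) = 1.45-fold (or exp(0.195) = 1.22-fold), and Welch on logs rejects just as often, about 39% (or 18%). With equal medians, rank-sum rejects in 5.1% to 5.4%. These rates reflect a real difference in location, not a fault particular to the test.

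Finally, choosing the test by preliminary checks, not analysing on the log scale, and not stating an effect estimate with an interval are matters of preference, or details that a condensed article may leave to the analysis plan. They are no part of this point.

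**Conclusion.** Wrong as written, in a limited sense. Read literally, section 4.6 prescribes an independent-samples rank test for paired data and offers it as a remedy for unequal variances. In the paired use the cost is power: at a 0.5 SD shift with 27 pairs, about 40% to 37% in place of 54% to 100%, with type I error of about 2% to 0%. The gap widens as the correlation rises. In the unequal-variance use the cost is a modest excess of false positives, about 5.6% to 7.4% with equal arms. The ranges rest on assumed correlations of 0.3 to 0.9, assumed SD ratios of 2 to 4 and normal data; the lognormal paired check agrees in direction.

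The paired defect bears most on the 60-minute HRV, on section 4.1's description of it as recorded in the experimental group only. The between-arm use for non-normal data of similar spread stands.

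**What to change.** Replace the fallback sentence in section 4.6 with three statements:

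- if paired differences are not normal, use the Wilcoxon signed-rank test;
- if variances differ between arms, use Welch's t-test;
- use the Wilcoxon rank-sum test only for the between-arm comparison of non-normal data with similar spread.

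If the present wording is a slip for signed-rank in the paired case, the same edit settles it. The cost is wording only, made before the data are analysed. Sample size, visits and data collection are unaffected.
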